**Methods:**

A randomised controlled trial (RCT) will be conducted to evaluate the efficacy and cost-effectiveness of a transdiagnostic CBT-based intervention for PPS. 322 participants with PPS will be recruited from secondary care clinics. Participants stratified by clinic and disability level will be randomised to CBT plus standard medical care (SMC) versus SMC alone. The intervention consists of 8 CBT sessions delivered by a qualified therapist over a period of 20 weeks. Outcomes will be assessed at 9, 20, 40- and 52-weeks post randomisation. Efficacy will be assessed by examining the difference between arms in the primary outcome Work and Social Adjustment Scale (WSAS) at 52 weeks after randomisation. Secondary outcomes will include mood, symptom severity and clinical global impression at 9, 20, 40 and 52 weeks. Cost-effectiveness will be evaluated by combining measures of health service use, informal care, loss of working hours and financial benefits at 52 weeks.

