### Proposed sample size

The sample size is based on a previous study: a RCT of rehabilitative treatments for chronic fatigue syndrome [20]. We used data from this trial as it also used the work and social adjustment as an outcome. Based on the White et al. study, we calculated a treatment effect of − 3.6 points on WSAS comparing CBT at 12 months. The within-group SD at 12 months was estimated to be 9.4 points giving a standardised effect size of Cohen’s d = 3.2/9.4 = − 0.38. The sample size calculation (Stata command sampsi) suggests that 161 patients per arm (322 in total) are needed to detect this effect size or a larger one with 90.14% power allowing for a deflation for including baseline measures in the analysis model (factor 0.84 assuming a correlation between baseline and 9-month WSAS of 0.4) and an attrition rate of 25%.

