### Statistical analysis

A statistical analysis plan (SAP) will be developed by the statisticians and agreed with the trial team before database lock. The formal statistical analyses will estimate the difference in mean outcomes between patients randomised to CBT plus SMC and SMC by intention to treat at the various post-treatment observation time points. Estimates of effect sizes together with 95% confidence intervals will be reported. It is planned that the main statistical analysis will use a linear mixed model with maximum likelihood estimation. The data will be analysed on an intention to treat basis.

The linear mixed model will contain post-treatment measures of the primary outcome (at the four follow up time points, i.e. 9, 20, 40 and 52 weeks) as the dependent variables. Fixed effects will consist of:
Baseline measures of WSAS;Trial arm;Dummy variables for time points (9, 20, 40 or 52 weeks);Trial arm Χ time interaction terms;Dummy variables for treatment clinic (randomisation stratifier).Dummy variable for disability level (randomisation stratifier)Dummy variables for therapist

Baseline measures of the outcome variable are included as they are known predictors of the outcome and thus should help us to gain precision for effect estimates of interest.

A random effect for participant will be entered into the model to account for correlations between the four repeated measures per participant. A more complex correlation structure (e.g. random intercept and slope model) may be considered if it proved to provide a better model fit.

Standardised effect sizes will be computed to measure the effect of treatment on primary and secondary outcomes at various assessment time points. This will be done by dividing the estimated trial arm difference by the baseline standard deviation of the measure.

We will investigate empirically whether non-adherence with CBT predicts loss to follow-up, and if this were the case, we will use multiple imputation instead of linear mixed modelling to generate inferences that are valid under a realistic missing at random assumption.

We will ensure that patterns of missing data and reasons for missingness are consistent with the CONSORT diagram. Baseline characteristics will be assessed to see if they predict missingness, if so, they will be included in the analysis model. We will check if any post randomisation variables such as compliance are predictive of missingness, and if so this will inform our missing data approach.

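### The default random-intercept model pools residual variance over four visits, so the standard error of the 52-week primary contrast is right only if week 52 has average variance

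*Protocol article*

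**What the plan says.** The abstract's Methods paragraph defines efficacy as the "difference between arms in the primary outcome Work and Social Adjustment Scale (WSAS) at 52 weeks after randomisation". The Statistical analysis section plans a "linear mixed model with maximum likelihood estimation" for the four follow-up measurements. Its listed fixed effects begin "Baseline measures of WSAS;Trial arm;Dummy variables for time points (9, 20, 40 or 52 weeks" and go on to "Trial arm Χ time interaction terms", the two stratifiers and therapist. Baseline WSAS therefore enters as one main effect, with no baseline-by-time term.

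On covariance the section says: "A random effect for participant will be entered into the model to account for correlations between the four repeated measures per participant". It continues: "A more complex correlation structure (e.g. random intercept and slope model) may be considered if it proved to provide a better model fit". It mentions neither visit-specific variances nor robust standard errors, and it gives no rule for judging fit.

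The only correlation in the article is in Proposed sample size: "factor 0.84 assuming a correlation between baseline and 9-month WSAS of 0.4".

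**The concern.** The arm-by-time terms give week 52 its own point estimate, but not its own variance. A random intercept implies one residual variance at all four visits and one correlation between any two of them. The 52-week standard error is therefore built from a four-visit average.

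Baseline commonly predicts an early visit better than one a year later. If that happens here and the SDs are similar, residual variance is smaller at week 9 and larger at week 52. The average then understates what the primary test needs. Growing SDs have the same effect. At stake are the coverage of the primary confidence interval and the false-positive rate of the only contrast that decides efficacy.

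**Working it through.** **Inputs from the article (Proposed sample size).** Effect 3.6 points; SD 9.4 at 12 months; baseline correlation 0.4 (variance factor 1 − 0.4² = 0.84); 161 per arm; 25% attrition. Two-sided 5% is assumed, because the Statistical analysis section says: "Estimates of effect sizes together with 95% confidence intervals will be reported".

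**The plan's own figure.** n = 161 × 0.75 = 120.75 per arm. SE = 9.4 × √0.84 × √(2/120.75) = 1.109. Power = Φ(3.6/1.109 − 1.96) = 90.1%, or 90.15% with n = 121. The stated 90.14% reproduces with 3.6 points. With the 3.2 printed in the effect-size fraction it would be 82.3%.

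**Assumptions not in the article.** The week-52 correlation with baseline is 0.4. Earlier correlations and visit SDs are varied. Between-visit correlation is either autoregressive (0.8) or exchangeable (0.7).

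**Closed form, complete data.** Let s_t be the visit SD relative to week 52, r_t the correlation with baseline, b_t = r_t·s_t, and b̄ the mean of the b_t.

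- True residual variance at visit t: v_t = s_t²(1 − r_t²) + (b_t − b̄)²
- Variance the model uses: the mean of the four v_t
- SE ratio, true to model: R = √(v_52 / mean v_t)
- Actual type I error: 2[1 − Φ(1.96/R)]

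Steep example, r = 0.70/0.60/0.50/0.40 with equal SDs: b̄ = 0.55 and v = 0.5325, 0.6425, 0.7525, 0.8625, with mean 0.6975. R = √(0.8625/0.6975) = 1.112, and the type I error is 2[1 − Φ(1.763)] = 7.8%. In WSAS points the model SE is 9.4 × √(2 × 0.6975/161) = 0.875, against a true 9.4 × √(2 × 0.8625/161) = 0.973.

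| Weeks 9/20/40/52 | mean v | v_52 | R | Type I error |
|---|---|---|---|---|
| r flat 0.4, equal SDs | 0.8400 | 0.8400 | 1.000 | 5.0% |
| r 0.50/0.47/0.43/0.40, equal SDs (mild) | 0.7975 | 0.8425 | 1.028 | 5.7% |
| r 0.60/0.55/0.45/0.40, equal SDs (moderate) | 0.7500 | 0.8500 | 1.065 | 6.6% |
| r 0.70/0.60/0.50/0.40, equal SDs (steep) | 0.6975 | 0.8625 | 1.112 | 7.8% |
| r flat 0.4, s 0.85/0.90/0.95/1.00 | 0.7218 | 0.8409 | 1.079 | 6.9% |
| moderate r, s 1.15/1.10/1.05/1.00 | 0.8651 | 0.8601 | 0.997 | 4.9% |
| r flat 0.4, s 1.15/1.10/1.05/1.00 | 0.9738 | 0.8409 | 0.929 | 3.5% |

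**With 25% loss** (monotone, completely at random, equal SDs, large sample):

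- Mild: 5.7–6.3%.
- Moderate: 6.8–7.4%.
- Steep: 8.1–8.7%. The largest SE ratio is 1.146, so the SE is 1 − 1/1.146 = 13% too small. Interval coverage is about 91–92%.

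**Simulated null trials of 322 patients with 25% loss** (Monte Carlo error about 0.5 points): mild 5.5–6.6%, moderate 6.6–7.7%, steep 7.8–8.8%. A run with flat correlations gave 5.9%, within two Monte Carlo errors of 5%.

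**Which feature causes it.** Giving baseline its own slope at each visit while keeping the random intercept still leaves 7.7% in the steep, complete-data case. Pooled variance accounts for nearly all of the effect.

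**Alternatives, same scenarios.**

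- Random intercept and slope: 4.2–5.0% in large samples, 3.4–5.1% in simulation.
- Unstructured covariance with baseline by visit: 5.0% in large samples, 3.9–5.3% in simulation. With 25% loss its 52-week SE is 1.06–1.08, so power is Φ(3.6/1.08 − 1.96) = 91.5% to Φ(3.6/1.06 − 1.96) = 92.5%.

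Clinic, disability and therapist dummies, and the possible switch to multiple imputation, were not modelled.

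**The case against.** The strongest reply is that the plan already names a remedy. A random intercept and slope model removes the inflation when it is used. If a likelihood-ratio test made the choice, it would pick that model in 88% of moderate trials with exchangeable correlation, and in essentially all steep or autoregressive ones. It would be picked rarely (21%) only in the mild exchangeable case, where the default itself runs at about 6%. Error under such selection was 3.4–5.3%. This stands: a plan that applied such a test would be nearly safe. But the article commits to no test. It says only that a richer structure may be considered, so the random intercept remains the default.

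It is also fair that the size rests on inputs the article lacks. Its 0.4 is attached to a 9-month measurement, close to week 40. With 0.4 at both weeks 40 and 52 and 0.6/0.5 earlier, the closed form gives 6.1%; with 0.5/0.45 earlier, 5.5%. The steep pattern is the upper end of the range.

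The analysis plan is not shown and may settle the covariance. The article does, however, state a default, and the comment is on that statement.

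A reader might infer three stronger things that the article does not support:

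- **That the trial's type I error is inflated as a matter of fact.** Better early prediction by baseline is not enough on its own; with falling SDs the moderate pattern gives 4.9%.
- **That the single baseline slope is a main cause.** It contributes almost nothing.
- **That dropout biases the 52-week estimate through the wrong covariance.** This is possible in principle, but no bias was quantified, and the article separately plans for predictors of missingness.

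**Conclusion.** The point holds in a conditional form. The default model's 52-week standard error is correct only if week-52 residual variance equals the four-visit average. With equal SDs, a week-52 correlation of 0.4 and a week-9 correlation between 0.5 and 0.7, the standard error is about 3–13% too small and a nominal 5% test runs at about 6–9%. Flat correlations and SDs leave it about right, and falling SDs can cancel or reverse the error. Nothing in the article shows which case will apply. The weakness is that protection depends on an optional choice, made after seeing the data, with no stated criterion. This is a worthwhile, cheap improvement and not a demonstrated failure of the trial.

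**What to change.** In the protocol or the analysis plan, replace the random intercept and its optional upgrade with one pre-specified primary model. It should have visit as categorical, arm by visit, baseline WSAS by visit and the remaining planned covariates, with an unstructured residual covariance for the four follow-ups, fitted by REML. Name a fixed order of simpler structures to be used only on non-convergence. If the random intercept is kept, pre-specify robust standard errors for the 52-week contrast.

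The cost is wording plus about 11 parameters: 10 covariance parameters in place of 2, and 3 extra baseline slopes. There is some risk of non-convergence, which the fallback order covers. Under the assumptions above, power for 3.6 points is about 92% with 25% loss, not below the planned 90.14%.

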### Economic evaluation

This analysis aims to compare the 1) service use and costs between CBT + SMC vs SMC, and 2) and assess the cost-effectiveness of CBT + SMC in relation to SMC. Two economic measures will be used to solicit data; i.e., the CSRI and the EQ-5D-5 L. The cost of services will be calculated by combining service use data with relevant unit costs [37–39]. Informal care and lost employment will both be valued using average wage rates. The use of services will be described by reporting the number of participants (%) accessing services in each group at different study points and the mean (SD) number of contacts for those using them (i.e. excluding those with zero use). Mean (SD) costs of individual services across the whole sample will also be reported and compared between the two study groups.

Health states data elicited using the EQ-5D-5 L will be combined with population utility weights to derive quality-adjusted-life-years (QALYs) used to measure health benefits in cost-utility analyses [40]. Cost-effectiveness will be assessed by combining the costs data (separately for each perspective) with the WSAS and QALYs. Incremental cost-effectiveness ratios will be computed and uncertainty around the results addressed using cost-effectiveness planes and acceptability curves.

### Trial oversight

The trial will be overseen by the Programme Management Group (PMG), as well as two independent committees, the Data Monitoring and Ethics Committee (DMEC) and the Trial Steering Committee (TSC). All committees will be responsible for ensuring that the study is conducted in accordance with the International Conference for Harmonisation of Good Clinical Practice guidelines. The DMEC will oversee the trial data, including serious adverse events and ethics and the TSC will monitor overall progress of the trial and ensure that the study protocol is being adhered to.

### Procedures for recording and reporting serious adverse events

Adverse Events (AE) will be assessed at 20, 40 and 52 weeks after randomisation. All serious adverse events (SAE) and reactions (SAR) will be reported immediately to the Chief Investigator, sponsor and DMEC. AE’s that are defined as serious will mirror the criterion described in a primary care cluster randomised controlled trial [21].

In summary, the reporting of SAE’s will be based on the following criterion; (i) death of a participant, (ii) life threatening event (iii) hospitalisation (not including elective hospitalisation for pre-existing condition) (iv) deliberate self-harm or (v) any important medical condition which may influence the participants safety. In addition, an SAE will be reported, if the participant deteriorates in that the level of disability worsens and they are unable.to carry out important daily activities for more than 4 weeks.

All serious adverse events and reactions will be reviewed, by two members of the DMEC without the presence of the CI. If deemed necessary, the scrutinisers would then be unblinded to treatment allocation so that they can then establish whether any serious adverse events were serious adverse reactions to the transdiagnostic approach.

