### Blinding

All data will be handled by the research team independent of the clinical team responsible for assessing and treating the patients. As this is a psychotherapy trial it is impossible to blind therapists and patients to which treatment they have been allocated to. Outcomes are all self-report measures and will be collected via post or email. Aside from the trial manger, the trial management team including the chief investigator, statisticians and the independent oversight committees will be blind to treatment allocation. If for any reason unblinding occurs the CI, TSC and DMEC will be notified.

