### Data collection and follow-ups

Outcome measures will be collected at baseline (pre-randomisation) and at 9, 20, 40, and 52 weeks post-randomisation. Outcome measures will be collected during a time window and will be dependent on the follow-up time-point. Time windows will be as followed; 9 weeks – (time-window 7, 12); 20 weeks – (time-window 18, 35); 40 weeks – (time-window 38, 49); 52 weeks – (time-window 50, 63).

Participants will be asked to complete self-report measures either in writing, electronically via email or over the telephone. If participants decline to complete the full follow-up assessment but have not revoked their consent to be followed up, they will be asked to fill in only the primary outcome questionnaires. Participants who do not return their questionnaires will be contacted by the research worker via telephone/text/email, to remind them to post back their questionnaires or to invite them to complete them over the telephone.

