### Measures

All measures are summarised in Table 2.

**Table 2 Tab2:** Screening and data collection across the trial

	Completed by	Baseline	End of Therapy	9 weeks	20 weeks	40 weeks	52 weeks
ASSESSMENTS							
Primary Outcomes							
WSAS	P	X		X	X	X	X
Secondary Outcomes							
PHQ-15	P	X		X	X	X	X
PHQ-9	P	X		X	X	X	X
GAD-7	P	X		X	X	X	X
PPS Questionnaire	P	X		X	X	X	X
CGI-patient	P	X		X	X	X	X
CSRI	P	X		X	X	X	X
EQ-5D-5 L	P	X		X	X	X	X
Process Variables							
Therapy Process Indicators							
*Treatment Attendance and Homework Log*^b^	T						
*Treatment Adherence*^b^	T						
*Treatment Fidelity*	IC		X				
*Competence Rating*	IC		X				
Satisfaction with Treatment^a^	P				X	X	X
CGI-therapist	T		X				
PSYCHLOPS^a^	P	X		X	X	X	X
Mechanisms of Change							
*CBRQ*	P	X		X	X	X	X
*Acceptance Scale*	P	X		X	X	X	X
Baseline							
Demographic Variables	P	X					
Clinical Information	P	X					
Preferred Treatment Group	P	X					
Therapist Background Measures	T	X					
Other							
Concomitant Medications	P	X		X	X	X	X
Serious/Adverse Events	P				X	X	X

*WSAS* work and social adjustment scale, *PPS Questionnaire* persistent physical symptoms questionnaire, *PHQ-9* patient health questionnaire – 9 item scale, *GAD-7* generalised anxiety disorder – 7 item scale, *PHQ-15* patient health questionnaire – 15 item scale, *CGI* clinical global impression scale, *CBRQ* cognitive behavioural responses questionnaire, *CSRI* client service receipt inventory, *EQ-5D-5 L* EuroQol 5 Dimension 5 Level, *PSYCHLOPS* psychological outcome profiles, *P* patient, *IC* independent clinician, *T* therapist. ^a^ Assessment only completed by participants assigned to the intervention group. ^b^ completed after each therapy session

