### Stopping rules

If deemed necessary, based on either new safety information or lack of recruitment, the trial may be prematurely stopped by the Sponsor, Chief Investigator, DMEC, TSC or Research Ethics Committee (REC). If the study is discontinued, participants enrolled onto the study will be informed and subsequently data collection will stop.

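### Adverse events are first asked about at week 20 (window weeks 18 to 35), although both arms already complete a 9-week pack, and no review of harms by arm during the trial is described

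*Protocol article*

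**What the plan says.** The section on recording and reporting serious adverse events fixes the schedule: "Adverse Events (AE) will be assessed at 20, 40 and 52 weeks after randomisation". Table 2 under Measures matches it. The row "Serious/Adverse Events" is patient-completed, marked at 20, 40 and 52 weeks and blank at 9 weeks. It carries no footnote limiting it to the intervention group, so both arms get the same question at the same times.

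Data collection and follow-ups states: "Outcome measures will be collected at baseline (pre-randomisation) and at 9, 20, 40, and 52 weeks post-randomisation". The 9-week window is weeks 7 to 12; the 20-week window is given as "time-window 18, 35".

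Serious events are to go immediately to the Chief Investigator, sponsor and DMEC. The criteria for a serious event include a deterioration in disability that stops important daily activities for more than 4 weeks.

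On oversight, the Blinding section says that, apart from the trial manager, "the trial management team including the chief investigator, statisticians and the independent oversight committees will be blind to treatment allocation". Two DMEC members review each serious event and may be unblinded, if deemed necessary, to judge whether it was a reaction to the intervention. The DMEC oversees serious adverse events (Trial oversight), is among the bodies that may stop the trial on new safety information (Stopping rules), and receives reports from the trial statisticians (Auditing).

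**The concern.** The schedule passes over a contact that already exists in both arms. In Table 2 every patient-completed follow-up measure is collected at 9 weeks except adverse events and the CBT-only satisfaction rating. Harms arising early in therapy are therefore first asked about when therapy is nearly or entirely over, and rest on long recall.

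The duty to report serious events immediately starts only once someone in the trial knows of the event. A death or an admission may become known by other routes. Sustained worsening of disability may leave no record outside the patient's own account, and it is a plausible early event in a therapy that includes exposure to avoided activities.

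Two further points bear on how harms are seen. CBT patients ideally meet a therapist every fortnight, while SMC patients have no matching trial contact, so events learned of between questionnaires could surface unequally. And case-by-case unblinding answers whether one event was a reaction; it does not show whether one arm has more events than the other. The Background describes a poor prognosis when PPS is untreated, so single cases of worsening are hard to attribute without comparing rates.

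**Working it through.** **Inputs (protocol article).**
- Adverse-event enquiry: weeks 20, 40 and 52 (serious-adverse-event section; Table 2).
- Windows: 9-week pack, weeks 7 to 12; 20-week pack, weeks 18 to 35; 40-week pack, weeks 38 to 49 (Data collection and follow-ups).
- Therapy period: 20 weeks (Abstract, Methods) or 22 weeks (Planned intervention). These two figures disagree and must be reconciled; both are carried below.

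**1. The plan's own schedule.** Text and Table 2 agree on 20, 40 and 52 weeks, so the stated schedule reproduces and there is no internal contradiction on it.

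**2. First recall as planned.** From randomisation to the 20-week form: 18 to 35 weeks by window, 20 weeks nominally. As a share of the 52-week follow-up: 20/52 = 38% nominally; 18/52 = 35% to 35/52 = 67% by window.

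**3. Gap after therapy.** Taking therapy to start at randomisation, the latest first enquiry falls 35 − 20 = 15 weeks after a 20-week course, or 35 − 22 = 13 weeks after a 22-week course. If therapy starts later than randomisation, the gap shortens by the same amount.

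**4. With the form also in the 9-week pack.**
- First recall: 7 to 12 weeks.
- Second recall: shortest 18 − 12 = 6 weeks, longest 35 − 7 = 28 weeks.

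**5. Later intervals, for comparison.** Between the 20- and 40-week forms: shortest 38 − 35 = 3 weeks, longest 49 − 18 = 31 weeks. Long recall is thus not confined to the first interval, but the first interval is the one that contains therapy.

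**6. By-arm oversight, sections side by side.** Blinding keeps the committees and the statisticians blind. Auditing makes the statisticians responsible for the DMEC's reports. The serious-event section allows unblinding for individual causality judgements. None of these describes a tabulation of harms by arm during the trial, and none forbids one: a table labelled A and B leaves its readers blind to which arm is which.

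**The case against.** The strongest reply is that this is a consistent design choice, not an error. The form is identical and identically timed in both arms, so late recall does not by itself favour either arm. Early deterioration is also measured symmetrically at 9 weeks through WSAS, PHQ-9, PHQ-15, patient-rated CGI, service use and concomitant medications. Serious events in either arm are reported at once, and SMC patients still see their specialists. All of that stands. It does not remove the point: the 9-week measures do not record adverse events, and nothing says that a worse 9-week WSAS prompts a check for a serious one.

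Three stronger readings are tempting and are not supported.
- *Harms will not be compared by arm.* The article does not say this. Blinding during the trial does not prevent a final comparison, which belongs to an analysis plan that is not at hand.
- *Harms are found unequally, biasing the safety comparison against CBT.* This is only a possibility. Therapists are given no adverse-event reporting role, and their session log lists no such item.
- *The DMEC cannot know the arm.* Two of its members may be unblinded for a given serious event. What is missing from the description is a view of rates.

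It may also be said that the content of DMEC reports is commonly left to a fuller document. That is fair, and limits the second part to asking that such a table exist.

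**Conclusion.** The point holds as a cheap improvement to harm ascertainment, not as a contradiction or a threat to the primary analysis. As written, harms during therapy are first asked about 18 to 35 weeks after randomisation, up to 13 to 15 weeks after therapy ends, when a contact at weeks 7 to 12 was available in both arms. The post-therapy gap assumes that therapy starts at randomisation and takes the end of the window.

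How many events would be missed or misdated cannot be estimated: the article gives no event rates and nothing on recall accuracy. Unequal detection through therapist contact is a possibility that the article neither shows nor rules out. On oversight, the supported conclusion is only that no by-arm review of harms during the trial is described.

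**What to change.** 1. **Add the existing adverse-event form to the 9-week pack in both arms**, for participants who have not yet passed week 9. The cost is one more page. The second recall interval may still reach 28 weeks. The trial registration entry says that recruitment has closed, so few or no participants may benefit; items 2 and 3 do not depend on this.
2. **Give the DMEC a closed table of serious adverse events by coded arm (A/B)**, prepared from data already held. This is compatible with the Blinding section. The cost is one table per report, and the coded split has to be supplied to whoever prepares it.
3. **Record the source of each report** (questionnaire, therapist, other) and keep all serious events, including deaths, in the main between-arm comparison. A sensitivity comparison limited to questionnaire-reported events can then show whether therapist contact affected detection. The main comparison should not be restricted that way: it would drop deaths and serious events in participants who return no form, and the sample size section allows for 25% attrition.
4. **Reconcile the 20- and 22-week therapy periods**, so that the adverse-event schedule can be read against one stated period.

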## Discussion

PPS are highly prevalent in both primary and secondary care, and are associated with severe physical disability, psychological distress and high health care costs [3, 4, 6]. This paper outlines the study protocol of an RCT designed to evaluate the efficacy and cost-effectiveness of a transdiagnostic cognitive behavioural intervention for adults with PPS in secondary care. The PRINCE Secondary study will be the first trial worldwide to address the efficacy and cost-effectiveness of a manual-based, transdiagnostic, approach for PPS. If it proves to be efficacious, this treatment approach could significantly improve overall functioning in patients with PPS and may lead to substantial long-term economic benefits to the NHS. Moreover, this approach could also be potentially beneficial for treating patients with other debilitating long-term conditions, including diabetes, hypertension and chronic kidney disease.

There are several limitations that need to be considered when assessing the potential impact and implications of our findings. First, we do not have an attention control so any change that occurs in the transdiagnostic CBT group cannot be attributed to the specific contents of the intervention. Second, the present trial protocol deviates from the original protocol. The intention of this study was to recruit a representative sample of therapists to deliver the intervention. However, only three therapists were recruited as opposed to eight which was outlined in the original protocol. This protocol deviation led to the trial becoming an evaluation of the efficacy of CBT delivered by these three therapists. This change in trial objective also led us to recalculate the sample size requirement with the approval of Camberwell St Giles REC.

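### Whether an SAE was a reaction to CBT may be decided after discretionary unblinding, with no blinded relatedness rating required first

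*Protocol article*

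**What the plan says.** Three parts of the protocol article bear on this.

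- **Procedures for recording and reporting serious adverse events.** Review covers every event: "All serious adverse events and reactions will be reviewed, by two members of the DMEC without the presence of the CI". The next sentence sets the order of unblinding and attribution: "If deemed necessary, the scrutinisers would then be unblinded to treatment allocation so that they can then establish whether any serious adverse events were". The class of event to be decided on, named where that sentence ends, is "serious adverse reactions to the transdiagnostic approach". Ascertainment is not limited to one arm: "Adverse Events (AE) will be assessed at 20, 40 and 52 weeks after randomisation".
- **Blinding.** Apart from the trial manager, "the trial management team including the chief investigator, statisticians and the independent oversight committees will be blind to treatment allocation". The section adds: "If for any reason unblinding occurs the CI, TSC and DMEC will be notified".
- **Measures, Table 2.** The footnote "Assessment only completed by participants assigned to the intervention group" is attached to treatment satisfaction and PSYCHLOPS. It is not attached to the row for serious and other adverse events.

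**The concern.** Whether therapy caused a serious event is a matter of opinion, and more so in this trial than in many. The SAE criteria include hospitalisation, deliberate self-harm and a worsening of disability that stops important daily activities for more than four weeks. Participants enter with a WSAS score of at least 10, and the Background describes marked impairment and a poor outlook without treatment. Such events can plausibly occur in either arm.

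The intervention also works through exposure and a return to avoided activities. A reviewer who knows that a participant had CBT might blame the therapy for a deterioration, or might put it down to the course of the illness. Either view is open to expectation, and knowing the arm lets that expectation in. At stake is the credibility of any statement about serious reactions to CBT. The reviewers are blind by default, so an opinion free of that influence could be had for almost nothing, but the stated procedure does not ask for one.

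**Working it through.** No arithmetic applies. The article gives no SAE rate, reaction rate or expected frequency of unblinding, so there is no figure to reproduce. The check is a reading of the sequence.

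1. **Who reviews what.** Two DMEC members review all SAEs and reactions, without the chief investigator. Nothing restricts this to one arm or to selected events.
2. **Blinding at the start of review.** The Blinding section keeps the oversight committees blind, so the first look at each SAE is blind by default.
3. **What comes next.** Unblinding follows the review and depends on being thought necessary. No criterion for necessity is given, and the text does not say whether unblinding covers one event or several.
4. **What unblinding is for.** Its stated purpose is to let the reviewers settle whether an SAE was a reaction to the intervention. Where it is used, attribution comes after knowledge of allocation.
5. **Whether an opinion is fixed beforehand.** Neither section requires one. The Blinding section requires only that unblinding be notified, which does not preserve what the reviewers thought before it.
6. **Whether attribution is always unblinded.** It is not. Unblinding is conditional. The article also has both SAEs and reactions reported immediately to the chief investigator, sponsor and DMEC, so a reaction label may exist before the DMEC review.
7. **Whether the control arm is observed.** It is. Adverse events are assessed at 20, 40 and 52 weeks with no limit by arm, the intervention-only footnote is absent from that row of Table 2, and the same two reviewers see all SAEs. Total SAEs can be compared between arms whatever attribution is made.
8. **What depends on the attribution.** The objectives list no reaction endpoint, and the Statistical analysis section plans no test of reactions. The primary analysis of WSAS does not use them.

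Steps 3 to 5 support the point. Steps 6 to 8 limit it.

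**The case against.** The strongest reply has four parts.

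- **A reaction to CBT can occur only in someone who received it, so allocation must be known in the end.** This stands. A count of zero reactions under SMC alone follows from the definition and is not evidence of bias. It does not require that clinical opinion be formed after allocation is known; the two steps can be separated.
- **Every SAE is first reviewed blind, and unblinding is the exception.** This stands. A reader might infer that causality is judged only once the reviewers are unblinded. The text does not say so.
- **SAEs are collected and reviewed in both arms.** This stands. A reader might infer that harms have no control-arm comparison. Table 2 and the SAE section contradict that. What the stated procedure does not yield is a comparison, by arm, of events that look treatment-related to a blind reviewer.
- **This is a condensed article, and review forms and unblinding triggers often sit in a fuller protocol or a DMEC charter.** This has some weight, and a missing form would not be a finding. But the article does not stay silent: it states an order, and that order puts attribution after unblinding. Its reference to a related primary care trial in this section is for the criteria of seriousness, not for how relatedness is judged. If a fuller document already requires a blinded rating, the remedy is only to align this sentence with it.

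**Conclusion.** The point holds in a limited form. Where the discretionary unblinding is used, relatedness to CBT is decided with knowledge of the arm, and no blinded opinion need be on record. Attribution of SAEs as reactions is therefore open to expectation, in a direction that cannot be predicted.

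The size cannot be put in numbers, because the article gives neither event rates nor how often unblinding would occur. Its reach is small: the comparison of total SAEs and the WSAS analysis are unaffected. It would be going too far to say that the trial's measure of harm is biased, since the article nowhere names the reaction count as its measure of harm and plans no analysis of it. The conclusion assumes that the article's sentence reflects the operating procedure and that no other document adds a blinded rating. It is a worthwhile low-cost improvement and not a serious fault.

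**What to change.** Replace the last sentence of the SAE section with a rule to this effect:

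1. For every SAE in either arm, each of the two reviewers records, before any unblinding and from a report redacted for allocation, whether the event would be considered related had the participant received CBT.
2. Allocation is then released for all events rated possibly related or higher, in place of release at discretion.
3. The final reaction classification is made with allocation known, and any change from the blinded rating is documented with its reason.
4. Report by arm both all SAEs and the blinded counts of possibly related events.

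The cost is an added field on the review form and redaction of the narratives; the same two reviewers do the work. Some narratives will still reveal that the participant had CBT, so blinding at this step will be imperfect. Sample size, follow-up schedule and primary analysis do not change.
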